*Data collection*: Household survey data were previously collected by trained interviewers using an electronic tablet-based survey tool and uploaded to a password-protected server. Trained data clerks will collect routine cohort data from routine patient records and will input this data daily into a predesigned database. Clinical audit data will be collected on a paper-based checklist from routine patient records and entered into a purpose-designed Excel spreadsheet. Cost data will be obtained from accounting records, supply orders and staff observation. Qualitative data will be collected by trained interviewers using topic guides. The adherence survey will utilise adapted pre-existing self-report medication adherence and beliefs measures with data entered into a purpose-designed Excel spreadsheet.

*Data analysis:* Secondary analysis of the pre-existing household survey data will use descriptive methods and multivariate regression modelling. For the cohort study, descriptive analysis and multivariate logistic regression analysis will be used to explore the clinical outcome trends, complication rates, quality of care and guideline adherence that occurred during implementation of this model. Data from the clinical audit and from the adherence survey will be analysed using descriptive statistics. Costing analysis will describe total and unit costs and will compare cost levels and trends across different time periods as new programmatic elements were added. The qualitative research will use thematic analysis. Qualitative and quantitative data from the various data sources will be triangulated.

**Ethical considerations:** This study protocol will be submitted to the MSF Ethics Review Board and LSHTM Ethics Committee for ethics clearance. Written authorisation to implement the study will also be obtained from the MoH of Jordan.

**Dissemination:** Ongoing data from the study will be shared with local, national (including the Jordanian MoH) and international stakeholders every 6 months in order to inform and improve the delivery of NCD care by MSF and other public health agencies in the study area. Outputs will include reports and peer-reviewed academic publications and presentations at key conferences and workshops.

Table of Contents

Key data 2

List of acronyms 3

Executive Summary 4

1. Background 12

1.1 MSF Model of NCD Care in Irbid 13

1.1.1 NCD Service 14

1.1.2 Patient circuit 15

1.1.3 MSF NCD Clinical Guidelines 18

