### 1.1.5 Programmatic Changes over Time

Specific additions were made to the programme over time in response to patient and programmatic needs. A home visit service, which commenced in August 2015, comprises a doctor, nurse and driver. It operates six mornings a week and serves frail or immobile patients living within a ten-kilometre radius of the clinics. 150 patients have been enrolled. They are seen on a monthly basis initially; stable patients may be reviewed by phone and visited less frequently.

A humanitarian liaison officer (HLO) was employed in August 2015 to assist vulnerable patients with social issues and direct them appropriately to services provided by other humanitarian actors. Patients are referred to the HLO by the medical team or the mental health service.

A mental health component was added in April 2016 to serve patients with NCDs and relevant, identified mental health co-morbidities, which may impact on their NCD care e.g. bereavement, anxiety or depression. Doctors and nurses can refer patients to the service. Two trained counsellors provide mental health and psychosocial support (MHPSS) through group psycho-education and discussion sessions and individual counselling. Group sessions take place in clinic waiting rooms and content is responsive to issues raised by patients. Individual sessions support patients’ medical treatment. Formal feedback structures between counsellors and medical staff have been introduced and will undergo review and refinement.

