| Maintenance  What are the challenges and facilitators for patients to remain in the programme?  What are the costs involved in maintaining the programme?  What are the programmatic challenges and adaptations made to maintain the programme? | Individual Level | Number/% of patients active 6 months post enrolment in reporting period  Numbers of medications and daily pill count at last consultation during reported period  Self-reported medication adherence rates and medication beliefs  Qualitative measure of individual-level maintenance:  Key challenges in maintaining medical treatment (including medication concordance)  Key challenges in altering lifestyle (diet, exercise, smoking)  Key mental health/ psychosocial challenges  Types of support available and strengths and challenges of the support (health education, MHPSS, HLO, family and community support) | Routine facility cohort data  Clinical Audit  Key informant interviews  2 Focus groups with patients  Semi-structured interviews with 12 MSF/clinic staff and 16 patients  Medicine/supply/staff costs  Staff time estimates  Self-report medication adherence questionnaire |
|  | Organisational Level | Measures of cost of maintenance  Institutionalisation of the programme/modifications made for maintenance  Alignment with organizational mission |  |

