### 3.4.2 Cohort study main outcome measures

The principal **clinical outcome measures** for patients in the cohort are:

DM: HbA1c < 7 or 8%; proportion of patients meeting individualised target at last visit within the reporting period and trend from baseline

Hypertension: BP < 140/90 mmHg: proportion of patients at target at last visit within the reporting period and trend from baseline

Cardiovascular disease: change in total cholesterol level from baseline

Asthma / COPD: Free from exacerbations / admissions in last six months

The principal **quality of care outcome measures** are the following:

Number/ % of active patients with CVD prescribed a statin during reporting period

Number/ % of patients with CVD prescribed aspirin during reporting period

Number/ % of patients with CVD prescribed at least one anti-hypertensive during reporting period

Number/% of patients with COPD/asthma with inhaler technique check documented

Number/ % of times when appropriate clinical action taken based on clinical or laboratory findings according to guideline (see Annexe 2e for detail)

Description of trends and patient characteristics in programme defaulters and deaths

Proportion of recommended referrals to other services that are appropriate as per guideline

Death is defined as confirmed death reported by family or community member. A defaulter is defined as a patient who has not attended any NCD clinic appointments within the last 90 days, is not known to have died or moved out of the area, and has not been successfully contacted by phone on two occasions by the clinic registrar. The definition was changed in October 2016 to reflect the newly extended appointment interval for stable patients to: two consecutive missed appointments; not known to have died, moved out of the area, or become immobile and ineligible for home care; and has not been successfully contacted by phone on two occasions by the clinic registrar.

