### 3.4.5 Cohort data analysis

Cohort data from both clinics will be aggregated and will be analysed using RStudio v1.0.136 (RStudio, Boston, MA 02210, USA). Descriptive statistics will be used to describe the patient cohort, explore clinical outcomes and analyse trends in outcome measures from baseline. To attempt to account for programmatic changes that occurred since the intervention began, comparison will be made between patients who entered the programme during different periods. Analysis will include proportions and means, presented with 95% confidence intervals (95%CI). Differences in proportions will be measured using Pearson χ2 test while differences in means will be measured using two-sample t-tests, presented with p-values. Clinical outcomes will be compared using multiple linear regression to explore the effect on key clinical outcomes of age, gender, origin (Syrian or Jordanian), economic status, mobility, type and number of morbidities (including relevant, identified mental health co-morbidity), and number of medications/pill burden.

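### The cohort regression is linear in section 3.4.5 but logistic in the Executive Summary, three of the four principal clinical outcomes are yes/no, and the listed predictors omit baseline value and length of follow-up

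*Protocol*

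**What the plan says.** Two places in the protocol name the regression model for the cohort.

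- Section 3.4.5: "Clinical outcomes will be compared using multiple linear regression to explore the effect on key clinical outcomes of age, gender, origin". The sentence goes on to list economic status, mobility, type and number of morbidities (with identified mental health co-morbidity) and number of medications or pill burden.
- Executive Summary, data analysis: "For the cohort study, descriptive analysis and multivariate logistic regression analysis will be used to explore the clinical outcome trends". That sentence also covers complication rates, quality of care and guideline adherence.

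Section 3.4.2 defines the principal clinical outcomes. For diabetes it is the "proportion of patients meeting individualised target at last visit within the reporting period and trend from baseline". For hypertension it is "BP < 140/90 mmHg: proportion of patients at target at last visit within the reporting period and trend from baseline". For asthma and COPD it is freedom from exacerbations or admissions over six months. For cardiovascular disease it is change in total cholesterol. Table 2 restates the cholesterol outcome as the share with a fall of at least 0.5 mmol/L.

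Two further places bear on the predictors. Table 2 lists, under Maintenance, "Numbers of medications and daily pill count at last consultation during reported period". Section 1.1.5 says: "A mental health component was added in April 2016".

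**The concern.** An analyst cannot follow both model statements for the same outcomes. A linear model of a yes/no outcome reports differences in proportion, and its usual standard errors assume a constant variance that such an outcome does not have. A logistic model reports odds ratios. If section 3.4.5 instead means HbA1c and blood pressure as measured values, the regression is not an analysis of the principal measures, and the text does not say so. The cohort data are retrospective, so an open choice of model or outcome scale can be settled after the results are visible.

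The predictor list raises a second problem. Section 3.4.2 takes the diabetes and hypertension outcomes at the last visit and asks for trend from baseline, yet neither the starting value nor the time between start and last visit is among the listed predictors. A coefficient for age or origin could then reflect how patients arrived, or how long they were followed, and not how they fared in the programme.

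**Working it through.** The protocol states no sample size, effect or precision for this regression, so there is no figure to reproduce. The check compares sections.

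**1. Outcome type (3.4.2 and Table 2)**

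| Principal clinical outcome | Form in 3.4.2 | Form in Table 2 |
|---|---|---|
| Diabetes: HbA1c target | yes/no | yes/no |
| Hypertension: BP target | yes/no | yes/no |
| CVD: total cholesterol | continuous change | yes/no (fall of at least 0.5 mmol/L) |
| Asthma/COPD: free from events | yes/no | yes/no |

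Three of four are yes/no under 3.4.2, and four of four under Table 2. The count concerns the principal clinical outcomes. Section 3.4.2 has a separate list of principal quality-of-care outcomes.

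**2. Model.** Section 3.4.5 says linear and the Executive Summary says logistic. Both refer to clinical outcomes of the same cohort.

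**3. Baseline value.** It is not among the predictors in 3.4.5. Section 1.1.6 records blood pressure at the first visit. Section 1.1.2 has cholesterol measured at the first visit, and HbA1c for known diabetics. Suppose older patients arrive with worse control and all ages improve equally. Without the baseline value, age will still be associated with missing the target at the last visit.

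**4. Length of follow-up.** It is not among the predictors. Section 3.4.3 uses files of patients admitted from January 2015 to December 2016, a span of 24 months, and section 3.4.1 requires only two visits. If the reporting period closes with that window, the last visit can fall anywhere from the second visit to about two years after enrolment.

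**5. Medication count.** Section 3.4.5 gives it no date. Section 1.1.6 records numbers and doses at the first and every later visit. Section 1.1.2 says medications are adjusted at follow-up on review of disease control. A later count is therefore partly a response to poor control, whereas a first-visit count precedes the follow-up outcome.

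**6. Mental health co-morbidity.** The service began in April 2016. January 2015 to March 2016 is 15 of the 24 admission months. Section 1.1.4 reports closure to new patients from May to October 2016. Counting those as six whole months leaves 24 − 6 = 18 open months, 15 of them before the service existed. Ascertainment may have been less complete in that period.

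**The case against.** The strongest reply is that this regression is exploratory. Sections 2, 3.4 and 6 disclaim any formal test of effectiveness, there is no comparator, and the principal measures will be reported mainly as proportions with 95% confidence intervals. That stands, and it limits the weight of the point.

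HbA1c, blood pressure and cholesterol are measured continuously, and 3.4.5 also plans means and t-tests, so linear regression is sound for those values. This also stands. A reader might infer that the linear model is wrong throughout; it is not. What remains is that 3.4.5 does not say it means the measured values, while 3.4.2 defines two of these outcomes as target met. The two model statements do not cover identical sets of outcomes either, but they overlap on the clinical outcomes.

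Covariate detail is often left to a statistical analysis plan, and the list in 3.4.5 does not forbid further adjustment. Section 3.4.5 also plans a comparison by period of entry, although not within the model. Table 2 gives versions of the HbA1c, blood pressure and cholesterol outcomes at 6 and 12 months, for which differing follow-up matters less. These points soften the covariate criticism. They do not reconcile the two model statements.

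Two stronger readings are tempting. One is that pill burden will be taken at the last visit. That timing belongs to a Maintenance indicator in Table 2, not to the covariate in 3.4.5. The other is that patients who left before April 2016 are coded as free of mental health co-morbidity, which would build in survivor bias. No coding rule is given, and histories and new diagnoses were recorded from the first visit. The documents support only possible under-ascertainment.

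**Conclusion.** The contradiction between section 3.4.5 and the Executive Summary is explicit, and the operative text does not match three of the four principal clinical outcomes. The absence of baseline value and follow-up time from the listed predictors makes the coefficients hard to interpret. The medication and mental health points concern timing that 3.4.5 leaves undated; they are grounds for dating the predictors, not proof of bias.

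No numerical size is claimed. Any figure for bias or lost precision would need correlations and success rates that the protocol does not give. The point should be corrected before the regression is run. It does not touch the descriptive proportions and does not put the evaluation's main results at risk.

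**What to change.** In section 3.4.5:

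- Use logistic (or modified Poisson) regression for target met and for exacerbation-free status. Keep linear regression for continuous HbA1c, blood pressure and cholesterol.
- Adjust for the baseline value where it is recorded: blood pressure, cholesterol, and HbA1c in known diabetics. Section 1.1.6 does not show a recorded six-month exacerbation history at entry, so baseline adjustment should not be promised for that outcome.
- Add enrolment period and months since enrolment to the model.
- Take number of medications or pill burden from the first visit.
- Add a sensitivity analysis that fits mental health co-morbidity in patients under follow-up from April 2016.

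Align the Executive Summary with this text. The cost is rewording two places and a small amount of extra analysis. First-visit blood pressure and medication numbers are listed in section 1.1.6, and first-visit cholesterol and HbA1c (known diabetics) in section 1.1.2. No new data collection is needed for these items.

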### 3.4.6 Clinical audit

A paper-based checklist (Annexe 2d) will be used by a trained clinical staff member(s) to evaluate a sample of two hundred patient files with ten per cent of the sample cross-checked by the medical supervisor. A randomly selected sample of files of patients enrolled in the programme for over 12 months will be used. In addition, 65 files (based on a precision of 10%) from amongst the patients with asthma will be randomly selected, since the active cohort contains fewer than 300 patients diagnosed with asthma. The data will be anonymised, entered by a trained data entry operator into a password-protected Excel software database, analysed using proportions measured with Pearson’s χ2 test and reported with 95% confidence intervals.

### 3.4.7 Costing analysis

A descriptive costing analysis will be undertaken to investigate total and unit costs, changes in these costs over time and the incremental costs of adding different components to this model of NCD care. We will describe the costs of implementing routine clinical review, providing medications and specific diagnostics e.g. spirometry, and the incremental costs of implementing the health education; mental health and home visit elements of the programme. Using an ingredients-based approach, the start-up, recurrent and capital costs will be determined, including the cost of supplies, room rental, transport, staff time and staff training. The cost analysis will take a health services perspective and will consider direct costs of alternative models of care.

Cost data for the drugs and supplies will be collected from routine accounting records and supply orders recorded in standard MSF budgeting and supply tools held by the MSF office in Irbid. Estimates of staff time spent on care and training will be collected by research staff through observation of care services in the two MSF clinics and discussions with relevant staff using a standardised methodology for calculating time estimates. These time estimates will then be converted to monetary values based on salary data held by the MSF office in Irbid.

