1. Patients who have an NCD other than those named above are not admitted to the programme but are referred to the MoH or other service providers where available e.g. isolated hypothyroidism is referred to the International Rescue Committee clinic.

2. Co-morbid NCDs in addition to those named above, which may be treated at primary care level with medications included in the MSF Essential Drug List, are managed within the programme e.g. providing analgesia for osteoarthritis pain or anti-acid medications for gastritis.

3. NCDs that are not managed by the programme currently e.g. cancer, or complications of the named NCDs requiring secondary or tertiary care input, are referred to MoH services or to other NGOs where available e.g. retinal screening for diabetic patients is provided by the Qatari Red Crescent hospital in Irbid.

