This evaluation, including use of routine service data, will take place in the two vertical, primary care based MSF-supported clinics providing NCD care in Irbid city centre. The first clinic was opened in December 2014 within an MoH primary care facility in Ibn-Sena. The clinic is located on the first floor, accessed by stairs only. The second clinic opened in April 2015, alongside a private organization, Arab Medical Relief (AMR), in their facility at Ibn-Rushd. This is located in the basement of a major civic building, also accessed by stairs only. Both clinics may be reached by public transport. Each contains a reception desk, central waiting area, triage room, individual consultation rooms, a larger room for group education sessions and a pharmacy. Ibn-Sena also has a treatment room where diabetic foot care is carried out.

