### 3.4.3 Cohort data sources

The cohort will use retrospective routine facility data collected from files of patients admitted from the start of January 2015 to the end of December 2016. Data on costs for the economic analysis will be obtained from logistics supply, accounting and pharmacy records, and from time estimates obtained through observation and discussions with staff (see below for more details).

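### Section 3.4.7 states a health services perspective and a look at alternative models, but the named cost sources support only the MSF programme's own cost

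*Protocol*

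**What the plan says.** Section 3.4.7 sets the scope in one sentence: "The cost analysis will take a health services perspective and will consider direct costs of alternative models of care". It then names its sources:

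- Drugs and supplies come from "routine accounting records and supply orders recorded in standard MSF budgeting and supply tools held by the MSF office in Irbid".
- Staff time comes from "observation of care services in the two MSF clinics and discussions with relevant staff".
- That time is "converted to monetary values based on salary data held by the MSF office in Irbid".

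Section 3.4.3 agrees: "Data on costs for the economic analysis will be obtained from logistics supply, accounting and pharmacy records", with staff-time estimates added. Section 1.1.6 lists only MSF tools as holding cost data.

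Elsewhere the costing is described more narrowly. The Executive Summary (Methods, Design) speaks of programmatic costs. In Table 2, the Implementation question asks what it costs to start and add to such a service, and the Maintenance question asks what it costs to keep the programme going.

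Section 1.1.1 describes care given outside the programme. Complications needing secondary or tertiary input go to the Ministry of Health or other NGOs, and "retinal screening for diabetic patients is provided by the Qatari Red Crescent hospital in Irbid".

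**The concern.** A perspective tells the reader whose costs are counted. A health services perspective ordinarily suggests that care falling on other public and NGO providers is included. Here that care is part of how the model works. The annual eye check for diabetic patients is a fidelity indicator in Table 2, and the audit checklist in Annex 2e accepts either a check done or a referral made. The protocol thus credits the model with care for which it collects no cost.

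The promise about alternative models raises a separate problem. It implies a comparison, but no comparator is named and no data are assigned to it.

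At stake is how the unit costs are read. Section 4.1 makes the findings available to the Ministry, NGOs and others planning similar programmes. A planner who takes the figure as the cost to the health service would use a number that leaves out referral care.

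**Working it through.** The protocol states no cost figure, referral volume or unit cost, so there is no figure to reproduce. The check sets each part of the stated scope against the sources named for it.

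| Part of the scope | Source named | What it covers |
| --- | --- | --- |
| Drugs and supplies | MSF budgeting, supply and pharmacy tools (1.1.6, 3.4.3, 3.4.7) | MSF programme |
| Staff time and training | Observation and discussion in the two MSF clinics, valued at MSF salaries (3.4.7) | MSF programme |
| Rent, transport and other inputs | Listed as ingredients in 3.4.7; accounting records in 3.4.3 | MSF programme |
| Added components (health education, mental health, home visits) | Same MSF sources (3.4.7) | MSF programme |
| Secondary and tertiary care at the Ministry or NGOs (1.1.1) | None | Not covered |
| Retinal screening at the Red Crescent hospital (1.1.1) | None | Not covered |
| Alternative models (3.4.7) | None, and none defined | Not covered |

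Three other places might have supplied the missing data:

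1. The cost row of Table 2 also lists key informant interviews and focus groups. Its indicators are staff time, start-up and recurrent costs, and unit costs. Nothing says the interviews collect other providers' costs.
2. The stakeholder topic guide (Annex 2d) mentions costs only as a prompt.
3. The adherence questionnaire (Annex 2f) asks whether medicines come from other sources, and from which type. It records no cost.

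The consequence can be written without numbers. Let M be the cost borne by MSF and E the cost of referred care borne by others, for the same patients and period. The full health-service cost is M + E. The named sources give M alone. Read as a health-service cost, the result is too low by the fraction E / (M + E). E is not observed, so the fraction cannot be calculated, and any percentage would be an assumption with no basis in the protocol.

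The Executive Summary (Data analysis) plans to compare cost levels and trends between periods. M can change because inputs change or because the split between M and E changes, and M alone does not separate the two. Table 2 already plans the trend in recommended referrals to other facilities as a proportion of the active cohort. That series would show whether the split may have moved, but it is not linked to the costing.

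**The case against.** The strongest reply is that the scope is already clear. The Executive Summary and Table 2 describe programme costs, and 3.4.7 speaks of components of this model. On that reading, a health services perspective means the cost to the service giving the care, as opposed to costs borne by patients or society, and MSF sources are the right ones. This reading is possible, and it is a good reason to restate the label rather than collect new data. It does not make the label safe, because 3.4.7 does not say which meaning applies.

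Alternative models might likewise mean the MSF model with and without its added parts. That is strained, since 3.4.7 already lists those incremental costs separately, but the protocol could adopt the meaning explicitly.

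Two stronger readings are tempting, and the documents support neither:

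- **Shifted cost passing for a saving.** A reader might infer that moving care to other providers will look like a saving. The protocol claims no saving, calls the costing descriptive, and in section 2 says it cannot assess cost-effectiveness. No section shows referral-out rising. The documented changes bring services in: home visits and the liaison officer from August 2015, mental health support from April 2016, and spirometry.
- **Uncosted host premises.** Because one clinic sits "within an MoH primary care facility in Ibn-Sena", a reader might infer that its premises go uncosted. Room rental is among the ingredients in 3.4.7, and nothing says the space is free of charge.

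**Conclusion.** The point holds as a mismatch between stated scope and available data. The sources named in 1.1.6, 3.4.3 and 3.4.7 can deliver the cost of the MSF programme to MSF. They cannot deliver the cost of referred care to other providers, or the direct costs of any alternative model.

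The direction is fixed by the design: if the result is read as a health-service cost, it omits whatever referred care costs. The size is unknown. The conclusion assumes that the sources listed are the sources to be used, and that the perspective would be read in its wider sense unless the protocol says otherwise.

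No clinical outcome, sample size or inferential analysis is affected. The correction should be made before the costing is reported, because it governs what the unit costs can be said to represent.

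**What to change.** In section 3.4.7:

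1. State the perspective as that of the provider, the MSF programme.
2. List externally delivered referral care (Ministry of Health, other NGOs, Red Crescent hospital) as excluded.
3. Delete the clause on alternative models, or limit it to the MSF model with and without its added components.
4. Show the referral trend already planned in Table 2 beside each period's unit cost, so that a change in referral-out is visible. It counts recommended referrals, so it signals volume only, not care received or its cost.

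This takes a few sentences and one added line in the cost table. Section 1.1.6 already records referral numbers, so no new data are needed. The downside is a narrower claim: the result would stand as programme cost and could not be presented as the cost of the model to the health service.
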